### 3.3. Sample size (required)

The final sample in this study will comprise at least 286 autistic adults (aged over 18) from across the globe.

### 3.4. Sample size rationale (optional)

#### 3.4.1. Replicating the regression analyses from previous research

In our regression analyses, we will include data for all participants that complete the study in one group (regardless of country of residence) to replicate the findings from previous studies [37, 58, 59] in a large and cross-cultural sample of autistic adults. The chosen sample size for these analyses is based on a series of sample size calculations conducted using G*Power [84], which focus on replicating the regression analyses of interest from Cage et al., [37], Perry et al., [59] and Hull et al., [58]. As a whole, we aim to verify whether experiencing a lack of autism acceptance predicts greater camouflaging and heightened depression and stress, and whether increased camouflaging predicts elevated anxiety (see Fig 1). Further details about the specific analyses can be seen below.

**Fig 1 pone.0261774.g001:**
[figure not shown]
A diagram showing the relationships that we will test in the current study. The plus (+) indicates a positive relationship between the variables and the minus (-) indicates a negative relationship.

Please note that for the following sample size calculations, we used an Bonferroni-adjusted alpha level of 0.0125 to account for multiple testing (4 regression analyses), and a power level of 90% (thereby giving us higher power than is standard in the field [85, 86]). To replicate the finding from Cage et al., that external acceptance and personal acceptance account for 17.5% variance explained in depression scores after controlling for age, gender, age of diagnosis, anxiety and stress (f^2^ = 0.37), 51 participants are required. In order to replicate the finding that external acceptance and personal acceptance account for 3% variance explained in stress scores after controlling for age, gender, age of diagnosis, anxiety and stress, 246 participants are required. To replicate the finding from Perry et al., that stigma significantly predicts camouflaging (f^2^ = 0.069) after controlling for age, gender, age of diagnosis, and autistic traits, 211 participants are required. Finally, in order to replicate the finding that anxiety accounts for 4% variance explained in camouflaging scores after controlling for age and autistic traits, 286 participants are required. Therefore, the final sample will comprise at least 286 participants (with full datasets).

#### 3.4.2. Comparing autism acceptance, camouflaging and mental health across cultures

In the analyses where we will compare participants’ experiences of autism acceptance, camouflaging, and levels of depression, anxiety and stress across countries, we will only include data from countries that have at least 30 participants (and therefore we will have sufficient data to draw comparisons between these multiple groups). We selected this cut-off as Sekaran [87] highlights that “where samples are to be broken into sub-samples…a minimum sample size of 30 for each category is necessary”. Importantly, Sekaran [87] also highlights that “in multivariate research…the sample size should be several times (preferably 10 times or more) as large as the number of variables in this study”. By recruiting at least 286 participants to our study, our sample is over 47 times larger than the number of variables in our multivariate analysis (6 variables: external acceptance, personal acceptance, camouflaging, depression, anxiety and stress), is as large as necessary based on our power analyses (largest sample size generated = 286), and would facilitate comparisons between participants in up to 9 countries.

## 4. Variables

*In this section you can describe all variables (both manipulated and measured variables) that will later be used in your confirmatory analysis plan. In your analysis plan, you will have the opportunity to describe how each variable will be used. If you have variables which you are measuring for exploratory analyses, you are not required to list them, though you are permitted to do so*.

### 4.1. Manipulated variables (optional)

Group membership–The autistic participants will be divided into groups based on the country in which they live (Australia, Belgium, Canada, Japan, etc.) in our Multivariate Analysis of Variance (MANOVA).

### 4.2. Measured variables (required)

#### 4.2.1. Demographic information

Participants will be asked a number of demographic questions to establish the nature of the sample. These will include questions about a) age, b) sex assigned at birth, c) gender identity, d) sexual identity, e) ethnicities, f) country of birth, g) country of residence, h) years lived in country of residence, i) level of education, j) how many siblings they have, k) income, l) co-occuring diagnoses m) how verbal they would consider themselves now, and n) how verbal they were as a child (as recommended by Botha, Hanlon and Williams [88]). Participants will also be asked to confirm whether or not they have an autism diagnosis, which diagnosis they received (e.g., Autism vs. Autism Spectrum Disorder), who gave them their diagnosis (e.g., multidisciplinary team, doctor, clinical psychologist, etc.), and finally the age they received that diagnosis. Those without a formal diagnosis will not be eligible to participate in the study.

#### 4.2.2. Autism acceptance

To measure perceptions of autism acceptance, we will use the six self-report autism acceptance questions outlined in Cage et al., [37]. First, in order to obtain a categorical response for acceptance, participants will be asked whether they feel that society (which will be specified as the general public, made up of people who do not personally know them) generally accepted them, with “yes”, “no”, “sometimes” and “prefer not to say” as response options. Second, participants will be asked to respond to the statement “over the past week, I have felt accepted by society as an autistic person/ person with autism”, on a five-point Likert scale from “strongly agree” to “strongly disagree”. Next, to measure perceptions of autism acceptance from different sources, participants will also be asked: “how accepted by society do you feel as an autistic person?”; “how accepted by your family and friends do you feel as an autistic person?”; and “how much have you personally accepted yourself as an autistic person?”. They will report their responses on a scale from zero, “not at all”, to ten, “completely”. Finally, in order to obtain qualitative responses, participants will have the opportunity to “tell us more about experiences of acceptance or non-acceptance” in an open text box. The English version of this set of autism acceptance questions has acceptable internal consistency (Cronbach’s α = 0.64) and good validity [37].

#### 4.2.3. Camouflaging of autistic traits

To measure the extent to which participants camouflage their autistic traits, we will use the Camouflaging Autistic Traits Questionnaire (CAT-Q; [51]). The CAT-Q comprises 25 items (e.g., “In social situations, I feel like I’m pretending to be normal”), rated on a seven-point Likert scale (ranging from one, “Strongly Disagree” to seven, “Strongly Agree”). Total scores on the CAT-Q can range from 25–175, with higher scores reflecting greater camouflaging. This self-report questionnaire assesses three different domains relevant to camouflaging: compensation (strategies used to compensate for socio-communicative difficulties, e.g., “I have spent time learning social skills from television shows and films, and try to use these in my interactions”); masking (strategies used to present a non-autistic or less autistic persona to others, e.g., “I monitor my body language or facial expressions so that I appear interested by the person I am interacting with”), and assimilation (strategies used to fit in to uncomfortable social situations, e.g., “I have to force myself to interact with people when I am in social situations”). The English version of the CAT-Q has strong psychometric properties, including internal consistency (Cronbach’s α = 0.94) and test-retest reliability (Pearson’s r = 0.77; [51]).

#### 4.2.4. Depression, anxiety and stress

To measure levels of depression, anxiety and stress, we will use the Depression, Anxiety and Stress Scale (DASS-21; [83]). In this 21-item questionnaire, participants judge whether certain statements (e.g., “I found it hard to wind down”) could be applied to their life over the past week on a scale from one to four (1 = “did not apply to me at all; 2 = “applied to me some of the time”; 3 = “applied to me a considerable degree”; 4 = “applied to me very much or most of the time”). The 21 items can be reduced to 7 items each for the depression, anxiety and stress subscales. Total scores for each subscale are calculated and multiplied by two (meaning that scores for each subscale range from 14 to 42), with higher scores representing higher depression, anxiety and stress. The DASS-21 has been previously used with autistic participants (e.g., [37, 89]) and the English [37, 89], French [90], and Japanese [91] versions have good internal consistency and factor validity.

#### 4.2.5. Questionnaires to facilitate our analyses in which we control for other participant characteristics

The following questionnaires are included to facilitiate a) the exploration of the relationships found previously between autistic traits and camouflaging, and alexithymic traits and mental health, and b) our analyses in which we control for these participant characteristics (see Exploratory Analyses).

#### 4.2.6. Autistic traits

The autistic traits of all participants will be assessed via the Autism Quotient (AQ; [92]). This self-report questionnaire assesses five different domains relevant to autistic characteristics (attention switching, attention to detail, communication, social skill and imagination). Participants are instructed to respond to 50 items with one of four responses: ‘definitely agree’, ‘slightly agree’, ‘slightly disagree’ and ‘definitely disagree’. These responses are scored using a binary system, where endorsing an autistic trait (either mildly or strongly) is scored as 1, and not endorsing an autistic trait (either mildly or strongly) is scored as 0. As such, scores on the AQ range from 0 to 50, with higher scores representing higher levels of autistic traits. The English [93], French [94], and Japanese [95] versions of the AQ have strong psychometric properties.

#### 4.2.7. Alexithymic traits

The alexithymic traits of participants will be measured via the 20-item Toronto Alexithymia Scale [96]. This self-report questionnaire comprises 20 items rated on a five-point Likert scale (from 1, strongly disagree, to 5, strongly agree). Total scores on the TAS-20 range from 20 to 100, with higher scores representing higher levels of alexithymic traits. The TAS-20 is the most popular tool for assessing alexithymia and the English [96, 97], French [98], and Japanese [99] versions have good psychometric properties.

#### 4.2.8. Translation of relevant questionnaires

Many of the questionnaires used in this study (e.g., the Depression, Anxiety and Stress Scale, the Autism Quotient, the Toronto Alexithymia Scale) have already been translated into the target languages (English, French, Japanese). However, other questionnaires (e.g., the Autism Acceptance Questions and the CAT-Q) are yet to be translated. We will follow the recommendations outlined in Gorecki et al., [100] for conducting translations for cross-cultural research. As such, we will use the forward-backward method of translation that has been used by other researchers in this field (e.g., [69]). The psychometric properties of the translated questionnaires will be assessed and reported in the manuscript (as was the case in Someki et al. [69]). More specifically, following the procedures outlined in Cage et al., [34] and Hull et al., [48], we will assess a) the internal consistency of the translated questionnaires via item analyses, and b) the factor structure of the translated questionnaires via principal component analyses.

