#### 5.1.2. Comparing autism acceptance, camouflaging and mental health across cultures

Finally, in order to compare participants’ experiences of autism acceptance, camouflaging, and levels of depression, anxiety and stress across countries, we will use a multivariate analysis of variance (MANOVA). This MANOVA will have the between-subjects factor *country* and the dependent variables *external acceptance*, *personal acceptance*, *depression*, *anxiety*, *stress*, and *camouflaging*. This will facilitate exploration of group differences in the levels of autism acceptance, camouflaging and mental health difficulties.

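### Internal consistency and PCA cannot detect a translation shift in mean scores, so a country difference involving a translated version could not be separated from translation

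*Protocol article*

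**What the plan says.** Section 4.2.8 separates instruments that already exist in English, French and Japanese from those that do not: "the Autism Acceptance Questions and the CAT-Q) are yet to be translated". For the latter it commits to a procedure ("we will use the forward-backward method of translation") that follows cited recommendations for cross-cultural work. It then names what will be assessed afterwards: "the internal consistency of the translated questionnaires via item analyses" and "the factor structure of the translated questionnaires via principal component analyses".

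The two instruments supply three of the six MANOVA outcomes: external acceptance, personal acceptance and camouflaging. Section 4.2.2 has one question on personal acceptance, answered from 0 to 10: "how much have you personally accepted yourself as an autistic person".

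Section 5.1.2 enters the six outcomes in a MANOVA with country as the factor and says: "This will facilitate exploration of group differences in the levels of autism acceptance, camouflaging and mental health difficulties". Section 5.3 tests it at 0.05. Section 3.4.2 admits a country with at least 30 participants. Section 1.2.2 predicts country differences for acceptance only; camouflaging and mental health are to be explored. Section 5.6 repeats the MANOVA with individual differences controlled and interprets what remains as cultural.

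No section states a language term, a restriction by language or a test of equivalence between versions, or makes the MANOVA depend on the psychometric checks. Section 5.2 standardises predictors, not outcomes by language.

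**The concern.** A comparison of means across countries needs a given answer to stand for the same level of the trait in each language version. The two named checks address a different matter: whether items hang together, and in what pattern, within a version. A translated scale can pass both and still read higher or lower than the English one.

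This is not a detail left to a later document. The protocol names its checks, and they are of the wrong kind for the comparison that follows.

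At stake is the interpretation of the cross-country aim. Section 1.1.3 hopes the comparison may help to identify regions for anti-stigma work and areas that need more mental health support. If a group that used a translation stands apart, the plan gives no means of telling country from translation. Acceptance is the most exposed outcome: it carries the only stated country prediction, and one of its two measures is a single item.

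**Working it through.** **1. The plan's own figures.** Section 3.4.2 supports the country comparison with 286 participants, six variables and a minimum of 30 per country. 286/6 = 47.7 and 286/30 = 9.5, so the stated ratio of over 47 and the limit of nine countries both reproduce. Neither figure bears on equivalence between language versions.

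**2. What the two checks can see.** Let a translation add a constant c_j to item j, so that y_j = x_j + c_j.
- Var(y_j) = Var(x_j) and Cov(y_j, y_k) = Cov(x_j, x_k).
- Cronbach's alpha = k/(k−1) × (1 − ΣVar(item)/Var(total)) uses only these terms, so it does not change. PCA uses the same covariance or correlation matrix, so it does not change either.
- The mean of the total moves by Σc_j.

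Numerical check with 25 simulated items, 2,000 respondents and every item raised by 0.35 (item SD about 0.99). Alpha was 0.963 before and after, and the largest change in any inter-item correlation was below 1e-15. The mean total moved by 0.48 SD.

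**3. The single item.** Alpha needs at least two items, and a PCA of one item is empty. Personal acceptance could be included in a PCA with the other acceptance questions, but by step 2 that says nothing about its mean.

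**4. Where version and country meet.** Section 3.2 lists sites in Belgium, Japan, the UK and the USA, with Australia, Canada and South Africa reached through Prolific. Section 4.2.8 gives the target languages as English, French and Japanese. That Japan would use Japanese and Belgium French is a reasonable inference, but no section says so. French could also be used in Canada.

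**5. Illustrative size.** Assumptions that are not in the documents: seven countries of 41 (286/7 = 40.9), no true country difference, and two countries shifted by d SD on one outcome.
- One-way test on that outcome alone: noncentrality λ = n·d²·m(k−m)/k, with n = 41, m = 2, k = 7. For d = 0.3, λ = 41 × 0.09 × 10/7 = 5.27 and the rejection probability is 35%. For d = 0.5, λ = 41 × 0.25 × 10/7 = 14.64 and it is 82%.
- Planned six-outcome MANOVA (Pillai, simulated, one outcome shifted): about 16% at d = 0.3 and 49% at d = 0.5, against 5%. The result depends on the correlation among outcomes. A rerun with 4,000 studies per setting gave 14% and 42% with uncorrelated outcomes, and 18% and 54% with all correlations at 0.3.
- One country shifted instead of two: the one-way test gives 21% and 57%; the MANOVA (correlations 0.3) gives 12% and 31%.
- Two countries shifted by only 0.2 SD: 16% for the one-way test and about 10% for the MANOVA (correlations 0.3).
- All three newly translated outcomes shifted in the same direction (correlations 0.3): 40% and 95% at d = 0.3 and 0.5.

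**6. What a shift in the CAT-Q total would take.** Assume three item blocks of 9, 8 and 8, loadings 0.65 and factor correlation 0.4. The variance of the total is 25 + 0.4225 × 184 + 0.169 × 416 = 173, so its SD is 13.2. One item shifted by 0.5 SD moves the total by 0.5/13.2 = 0.04 SD. A material shift therefore needs many items to move in the same direction. The single acceptance item has no such protection.

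**The case against.** The strongest reply is that forward-backward translation under published recommendations is the step meant to preserve meaning, and that a shift of 0.3 to 0.5 SD is supposed, not shown. This stands in part. The procedure lowers the risk, but it does not test for a shift, and the checks that follow cannot find one.

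A second reply is that the harm is conditional. A shift must exist, version must largely follow country, and Japan or Belgium must reach 30 participants to enter the MANOVA. This stands, and it limits the wording. A reader might infer that translation shifts will be reported as cultural differences; the documents support only that they could be. Section 1.1.3 likewise speaks of potential uses, not of a decision rule.

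A reader might also take the preference in section 3.4.2, "the sample size should be several times (preferably 10 times or more) as large as the number of variables in this study", to require 250 respondents per language for a PCA of the 25-item CAT-Q. The documents do not support that. The protocol applies the rule to six MANOVA outcomes and the total sample, the minimum of 30 governs entry to the MANOVA, and no sample size for a PCA is stated.

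Finally, it may seem natural to call a difference cultural only if it appears among the English-speaking countries. That would be unsound. A genuine difference for Japan or Belgium could never qualify, and a difference between, say, the UK and the USA says nothing about Japan.

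**Conclusion.** The point holds in conditional form. The two checks cannot show that mean scores are comparable across language versions; this follows algebraically and needs no assumption. Neither check can be computed for personal acceptance alone. If version largely follows country and a translated-version country enters the MANOVA, country and translation are mixed and the plan has no way to separate them.

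The 16% to 49% range illustrates the planned MANOVA under the assumptions in step 5 and is not an estimate for this study. The higher 35% to 82% range belongs to a one-way test of a single outcome, which is not the planned test, and should not be quoted as the error rate of the plan. The cross-country interpretation should be repaired before data collection.

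**What to change.** 1. Record the language version each participant completed. Section 3.1 says that no data have been collected, so this can start with the first participant.
2. Pre-specify a sensitivity MANOVA restricted to respondents who completed the English versions, defined by language and not by country of residence.
3. State that contrasts between language versions, above all on the single acceptance item, will be reported as country/language differences that cannot be separated from translation, and not as cultural differences. Carry the same wording into the adjusted MANOVA in section 5.6.
4. Optionally, add an item-level comparison of the CAT-Q across versions (item bias given total score). Say with it that it detects shifts specific to some items but not a shift common to all. In a simulated shift of all items (0.57 SD in the total, 41 translated against 205 English respondents), items were flagged at 5.2%, which is the nominal rate.

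The cost is one recorded field, one repeated analysis and some protocol wording. The drawbacks are more cautious conclusions for translated-version countries and a smaller sample in the sensitivity analysis: 5 × 41 = 205 of 287 under the illustration, if five of the seven countries used English.

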## 5. Analysis plan

*You may describe one or more confirmatory analysis in this preregistration. Please remember that all analyses specified below must be reported in the final article, and any additional analyses must be noted as exploratory or hypothesis generating*.

*A confirmatory analysis plan must state up front which variables are predictors (independent) and which are the outcomes (dependent), otherwise it is an exploratory analysis. You are allowed to describe any exploratory work here, but a clear confirmatory analysis is required*.

### 5.1. Statistical models (required)

First, in our regression analyses, we will include data for all participants that completed the study in one group (collapsing across countries) to explore relationships in a large and cross-cultural sample of autistic adults. For these four regression analyses, we will use a p < .0125 threshold to establish whether to reject the null hypothesis (corrected for multiple testing). Then, we will separate participants into groups based on their country of residence and compare participants’ experiences of autism acceptance, camouflaging, and levels of depression, anxiety and stress across these groups.

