### 5.3. Inference criteria (optional)

For our regression analyses, to account for the four tests we will use a p < .0125 significance threshold to determine whether to accept or reject the null hypothesis. For our MANOVA, we will use a p = .05 significance threshold.

In our analyses, Bayes Factors (BF_01_) may be reported, which provide a ratio of the likelihood for the observed data under the null hypothesis compared to the alternative hypothesis [101]. For all Bayesian analyses, we will follow the classification scheme in JASP outlined by Lee and Wagenmakers [102]: BF_10_ values between one and three will be considered as weak evidence, between three and ten as moderate evidence and greater than ten as strong evidence for the alternative hypothesis.

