### 5.6. Exploratory analysis (optional)

We will explore the relationships between our dependent variables (external acceptance, personal acceptance, depression, anxiety, stress and camouflaging) and various individual differences (e.g., autistic traits, alexithymic traits, gender, level of education, age of diagnosis, income etc.). For continuous variables, we will run simple (Bonferroni-corrected) correlations between our dependent variables and demographic factors (e.g., age, autistic traits). For categorical variables, we will use Bonferroni-corrected independent samples t-tests to compare levels of autism acceptance, camouflaging and mental health difficulties across the demographic factor (e.g., gender). For example, as gender is a categorical variable, we will use Bonferroni-corrected independent samples t-tests to compare levels of acceptance, camouflaging and mental health across genders. Conducting these analyses will allow us to verify whether any individual differences are associated with any of our dependent variables as has been found previously in some instances (e.g., camouflaging and gender; [41]).

Then, we will conduct our MANOVA again whilst controlling for any of the individual differences that are associated with our dependent variables or which differ significantly between groups. This will allow us to determine whether there are cultural differences in autism acceptance, camouflaging and mental health that go beyond these specific individual differences.

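### Holm's step-down procedure would be a cheap improvement on the fixed p < .0125 rule for the four confirmatory regressions; the rule itself is not an error

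*Protocol article*

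**What the plan says.** Section 5.1 of the protocol article sets one fixed threshold for all four regressions: "For these four regression analyses, we will use a p < .0125 threshold to establish whether to reject the null hypothesis". Section 5.3 repeats it: "to account for the four tests we will use a p < .0125 significance threshold to determine whether to accept or reject the null hypothesis".

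The sample-size rationale in section 3.4.1 uses the same level: "we used an Bonferroni-adjusted alpha level of 0.0125 to account for multiple testing (4 regression analyses), and a power level of 90" per cent. The sample sizes it reports are 51 (depression), 246 (stress), 211 (camouflaging) and 286 (anxiety and camouflaging). The largest becomes the minimum recruitment.

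The MANOVA is tested separately at .05 and lies outside this family. Section 5.6 applies Bonferroni to the exploratory correlations and t-tests. No step-down procedure is mentioned.

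**The concern.** Under the fixed rule each test must reach .0125 whatever the other three show. Holm orders the four p-values and compares them in turn with .05/4, .05/3, .05/2 and .05, stopping at the first failure. Its family-wise error is at most 5% under any dependence, and it rejects everything that Bonferroni rejects.

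The difference has practical weight here because the four tests are very unequally powered. Depression needs 51 participants and at least 286 are planned, so that test is almost sure to reject. Once it does, the other three start at .0167 under Holm but stay at .0125 under the plan. At stake is some power for the stress, camouflaging and anxiety tests, with no change in sample size or family-wise error bound.

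**Working it through.** **Inputs from the protocol article**
- Family of four tests, per-test alpha .0125, power 90%, planned N of at least 286 (sections 3.4.1, 5.1, 5.3).
- Depression: "after controlling for age, gender, age of diagnosis, anxiety and stress (f^2^ = 0.37), 51 participants are required". Two tested predictors out of seven (section 5.1.1).
- Stress: "external acceptance and personal acceptance account for 3% variance explained in stress scores", N = 246, two tested of seven. No f² is given.
- Camouflaging: "that stigma significantly predicts camouflaging (f^2^ = 0.069) after controlling for age, gender, age of diagnosis, and autistic traits, 211 participants are required". One tested of five.
- Anxiety and camouflaging: 4% of variance, N = 286, one tested of three. No f² is given. The sample-size text puts camouflaging as the outcome and section 5.1.1 puts anxiety. With the same covariates the partial F test is the same either way.

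**Step 1: reproduce the plan's figures.** The threshold is .05/4 = .0125. For the sample sizes, use the noncentral F test for an increase in R², with u tested predictors, v = N − k − 1 for k predictors in total, and λ = f² × N. At alpha .0125:
- f² = .37, u = 2, k = 7: power is .904 at N = 51 and .897 at N = 50, so 51 is reproduced.
- f² = .069, u = 1, k = 5: power is .901 at N = 211 and .8997 at N = 210, so 211 is reproduced.

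The other two sample sizes cannot be checked fully without f². Solving for the f² that gives 90% power yields .0695 (stress, N = 246) and .0505 (anxiety, N = 286). These are assumptions. The 90% for anxiety at N = 286 follows from this construction and is no independent check.

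**Step 2: power at N = 286 under each rule.** Bonferroni tests each p-value at .0125. Holm uses .0125, .0167, .025 and .05 on the ordered p-values. Four F statistics were simulated as independent.

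| Test | f² | Bonferroni | Holm |
|---|---|---|---|
| Depression | .37 (stated) | 1.00 | 1.00 |
| Stress | .0695 (back-solved) | .945 | .982 |
| Camouflaging | .069 (stated) | .973 | .992 |
| Anxiety | .0505 (back-solved) | .900 | .965 |

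With all four nulls true, the simulated family-wise error is .049 for both rules.

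**Step 3: a less favourable reading of the unstated effects.** Converting the percentages as f² = R²/(1 − R²) gives .03/.97 = .0309 for stress and .04/.96 = .0417 for anxiety. Power then rises from .565 to .746 (stress) and from .825 to .914 (anxiety). Camouflaging goes from .973 to .990.

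**Step 4: dependence.** The regressions share participants and variables, so independence is not realistic. A large-sample chi-square approximation with the Step 2 effects and one common correlation of 0, .3, .6 or .9 between the statistics gives anxiety power of .904 under Bonferroni and between .960 and .966 under Holm. Stress goes from .949 to between .973 and .984. The size of the gain moves a little; its direction does not.

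**The case against.** The strongest reply is that nothing needs correcting. Bonferroni is valid and prespecified, and it is stated the same way in sections 3.4.1, 5.1 and 5.3. Its cost is already paid in the planned N, so on the plan's inputs as back-solved each test has at least 90% power at .0125. That stands.

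A reader might go further in four ways that the document does not support:

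- **That power is thrown away for nothing, or that Holm is uniformly more powerful.** Holm's first step is also .0125, so it gains nothing for the smallest p-value, nothing when no other test rejects, and nothing for depression. A fixed threshold keeps each replication verdict independent of the other three and gives simple matching intervals, although the protocol does not offer these as reasons.
- **That the plan misses a joint target.** With the Step 2 inputs, the power to reject all four is about .83 under Bonferroni and .94 under Holm. But section 1.2.1 makes separate predictions and section 5.3 judges each regression on its own. The remark in section 3.4.1 about the aims as a whole summarises them and sets no all-four success criterion.
- **That the power figures are firm.** Two of the four f² values are not stated, and the main table assumes independence.
- **That section 5.6 needs the same change.** Those analyses are labelled exploratory, and no gain has been calculated for them.

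**Conclusion.** The point holds as an optional, low-cost improvement. It is not an error, a contradiction or a shortfall in planned power. Holm keeps the 5% family-wise error under any dependence and never rejects less than the present rule; neither property rests on the power assumptions.

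The size of the gain does rest on them. With the back-solved effects it is about 6.5 percentage points for anxiety, 4 for stress, 2 for camouflaging and none for depression. If the stress and anxiety effects are as small as the direct conversion of 3% and 4% implies, it is about 18 points for stress (.746 − .565) and 9 for anxiety (.914 − .825). The gain is therefore largest where the sample-size inputs are least secure.

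**What to change.** In sections 5.1 and 5.3, replace the fixed p < .0125 rule by Holm's procedure at family-wise 5% over the four regression tests, one p-value per regression as the present count of four implies. Leave the sample-size text in section 3.4.1 at .0125, where it is then conservative. Applying Holm in section 5.6 is optional.

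The cost is one sentence in each of the two sections, with no extra participants. Section 3.1 says that no data have been collected, so the change can still be made in advance of any results.

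The one real downside concerns intervals. Simultaneous confidence intervals that match Holm are less direct. If 98.75% intervals (1 − .0125) are kept for reporting, one may include zero for an effect that Holm declares significant. The text should therefore say that the Holm-adjusted p-value decides and that the intervals are descriptive.
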